## Abstract

**Background:**

Comorbidity between problem gambling and depression or anxiety is common. Further, the treatment needs of people with co-occurring gambling and mental health symptoms may be different from those of problem gamblers who do not have a co-occurring mental health concern. The current randomized controlled trial (RCT) will evaluate whether there is a benefit to providing access to mental health Internet interventions (G + MH intervention) in addition to an Internet intervention for problem gambling (G-only intervention) in participants with gambling problems who do or do not have co-occurring mental health symptoms.

**Methods:**

Potential participants will be screened using an online survey to identify participants meeting criteria for problem gambling. As part of the baseline screening process, measures of current depression and anxiety will be assessed. Eligible participants agreeing (*N* = 280) to take part in the study will be randomized to one of two versions of an online intervention for gamblers – an intervention that just targets gambling issues (G-only) versus a website that contains interventions for depression and anxiety in addition to an intervention for gamblers (G + MH). It is predicted that problem gamblers who do not have co-occurring mental health symptoms will display no significant difference between intervention conditions at a six-month follow-up. However, for those with co-occurring mental health symptoms, it is predicted that participants receiving access to the G + MH website will display significantly reduced gambling outcomes at six-month follow-up as compared to those provided with G-only website.

**Discussion:**

The trial will produce information on the best means of providing online help to gamblers with and without co-occurring mental health symptoms.

**Trial registration:**

ClinicalTrials.gov NCT02800096; Registration date: June 14, 2016.

## Background

It is estimated that up to half of pathological gamblers have co-occurring mental health symptoms (e.g., depression or anxiety disorder) [1–6]. While there is little work in this area, co-occurring mental health symptoms are thought to impact on the treatment needs of problem gamblers [7–12]. The interrelationship between problem gambling and co-occurring mental health symptoms may not have the same cause for all those experiencing these co-occurring conditions. For some, gambling may be an attempt to alleviate the symptoms of depression and anxiety [13]. Others may experience symptoms of anxiety and depression as a result of increasing difficulties with gambling (financial or otherwise) [14]. For others, while occurring simultaneously, problem gambling and co-occurring mental health symptoms may not be causally related (or both might be the result of some third factor) [15]. In addition, it is important to consider the extent to which the interrelationship between problematic gambling and co-occurring mental health symptoms varies by gender – both in the strength of the observed relationship as well as in the underlying mechanisms that are driving this interrelationship [2, 16]. Further research employing longitudinal designs is needed to develop a better understanding of these interrelationships [5, 12, 17].

While the functional relationship of gambling to co-occurring mental health symptoms is an important research question, the goal of the present trial is a pragmatic one and, as such, does not need to wait upon a better understanding of these interrelationships. We seek to determine whether providing simultaneous access to online help for gambling problems and mental health symptoms is of benefit for those experiencing both concerns (and, to a lesser extent, that providing simultaneous access is not disadvantageous for those with just a gambling problem and no co-occurring depression or anxiety symptoms). A secondary goal will be to determine if there are moderators (e.g., gender, extent of use) for the hypothesized benefit of providing the G + MH intervention website to those problem gamblers with co-occurring mental health symptoms.

### The need for alternatives to face-to-face care

The large majority of problem gamblers will never access traditional treatment [18–20]. Barriers include stigma, availability, and a desire for self-reliance [21]. The Internet is widely available and has been recognized as an important platform through which to decrease treatment-seeking stigma, and to provide evidence-based care in an accessible and cost-efficient fashion [22]. Despite being unwilling, or unable to attend traditional treatment, many problem gamblers have voiced an interest in accessing help through other means, such as the Internet [23].

### Self-help for gambling

There is a growing evidence base for self-help interventions targeting gambling – primarily through bibliotherapy with or without limited contact with a therapist [24, 25]. To increase the accessibility of such interventions, some efforts have also been made to provide Internet-based self-help materials for problem gamblers [26, 27]. However, these online interventions have little or no published evidence base and relevant issues, such as the best way to provide such services to people with co-occurring mental health symptoms have, as yet, not been addressed.

## Major research questions

The proposed trial will compare two Internet intervention websites – an intervention that just targets gambling issues (G-only) versus one that contains interventions for anxiety and depression in addition to an intervention for gamblers (G + MH). The primary hypotheses are:**Hypothesis 1:** For problem gamblers with co-occurring mental health symptoms, it is predicted that participants provided access to the G + MH website will display significantly reduced gambling outcomes at three- and six-month follow-ups as compared to those provided access to the G-only website.**Hypothesis 2:** Problem gamblers without co-occurring mental health symptoms will display no significant difference between the G-only and G + MH websites at three- and six-month follow-ups.**Hypothesis 3:** Respondents who have more involvement with the G-only intervention between baseline and three-month follow-up will demonstrate more improvement in gambling outcomes at six-month follow-up, compared to respondents who have less involvement with the G-only intervention.

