### Power analysis

We propose to collect a sample of 280 participants and we estimate that we will successfully follow about 224 participants at six months (20 % attrition) [34]. This number will also provide sufficient power to conduct the proposed statistical tests comparing hypotheses, based upon gambling frequency and NODS data from Hodgins et al. [33, 34], assuming a correlation of .5 between baseline and follow-up values, power = .80 and an α = .05. This sample size will be sufficient to detect a difference of about two gambling days per month between conditions at each follow-up interval. Smaller differences may not be clinically important. Similarly, this sample size will be sufficiently powered to detect a 1 point difference on the NODS at six months. These calculations are based upon a repeated measures ANOVA model. The proposed analyses will employ mixed effects repeated measures models and, as such, will have greater statistical power because all observed data are included.

Also important is to ensure that there are enough females in the sample to conduct the proposed sex difference analyses. Approximately a third of problem gamblers in the general population are female [47]. With the assumption that this proportion would be maintained in our sample (i.e., those who would be concerned about their gambling and agree to participate in the study), roughly 92 of the 280 respondents will be female. A sample with 23 respondents per condition is sufficiently large to conduct the proposed analyses. However, our experience using these same recruitment methods in other studies is that females tend to be more interested in self-help materials than males and also, to be willing to participate in the proposed research. Thus, we fully anticipate that more than a third of respondents will be female (perhaps as many as half will be female if the recruitment trends in our other studies hold true with this trial as well).

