### Data analysis

Analyses for Hypotheses 1 and 2, comparing outcomes between groups, will employ mixed effects repeated measures models that use all available data for each participant. Separate analyses will be conducted for each primary outcome variable. This same analytic approach, with the addition of interaction terms, will be used for secondary analyses examining moderators (e.g., extent of use, gender). Missing data will be handled using a maximum likelihood approach to estimate covariances, variances and means.

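### Hypothesis 2 is worded so that a non-significant test supports it, which cannot show that G + MH does no harm; it needs a non-inferiority form with a justified margin

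*Protocol article*

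**What the plan says.** The Protocol article, Major research questions, lists three primary hypotheses. The second is that "Problem gamblers without co-occurring mental health symptoms will display no significant difference between the G-only and G + MH websites" at three and six months. The Abstract repeats the prediction for six months.

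The Background gives the purpose, ranked below the main aim: to establish that "providing simultaneous access is not disadvantageous for those with just a gambling problem".

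Under Data analysis, one approach serves both hypotheses: "Analyses for Hypotheses 1 and 2, comparing outcomes between groups, will employ mixed effects repeated measures models", with a separate analysis for each primary outcome. Under Follow-up assessments, the primary outcomes are NODS score and gambling days per month.

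The Power analysis section plans 280 randomised and about 224 followed at six months, "assuming a correlation of .5 between baseline and follow-up values, power = .80 and an α = .05". On gambling days it says "This sample size will be sufficient to detect a difference of about two gambling days per month between conditions at each follow-up interval", adding that "Smaller differences may not be clinically important". On severity it says "this sample size will be sufficiently powered to detect a 1 point difference on the NODS at six months".

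**The concern.** The question is one-directional: does adding MoodGYM make things worse for gamblers without depression or anxiety symptoms? The stated prediction is the absence of a significant difference. These do not match, for three reasons.

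- Failing to reject the null does not bound the difference. The confidence interval may still include a harm that matters.
- The incentive is reversed. Fewer participants, more dropout and noisier measurement all make the prediction easier to fulfil.
- A significant benefit of G + MH would contradict the hypothesis as worded, although benefit is fully compatible with no harm.

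At stake is a conclusion attached to a primary hypothesis, which could rest on absence of evidence.

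**Working it through.** **Inputs from the Protocol article.** 280 randomised, 20% attrition, power 0.80, α = .05, detectable differences of 2 days and 1 NODS point (Power analysis); about 50% of the sample with co-occurring symptoms, defined by a K10 cut-off of 22 (Inclusion criteria).

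**Assumptions.** 1:1 allocation, a two-sided test, a normal approximation and equal attrition across strata. None of these is stated.

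**The plan's own figures.** 280 × 0.80 = 224 followed, which agrees. The 80% power cannot be reproduced: the article gives no SD and does not say whether the power refers to all 224 or to one symptom stratum. I therefore solved backwards under both readings.

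**Stratum size for Hypothesis 2.** 224 × 0.5 = 112, or 56 per arm.

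**Standard error implied by 80% power at 2 days.** 2 / (1.960 + 0.842) = 2 / 2.802 = 0.714 days.
- Whole-sample reading: 0.714 is the SE with 112 per arm (residual SD 0.714 × √56 = 5.34 days). In the stratum the SE is 0.714 × √2 = 1.010.
- Per-stratum reading: 0.714 is already the stratum SE (residual SD 0.714 × √28 = 3.78 days).

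For NODS at 1 point every quantity halves, so the probabilities below are identical.

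**Chance of a non-significant result when the true harm is 2 days (or 1 point), per outcome and time point.** Approximately Φ(1.96 − 2/SE).
- Whole-sample: Φ(1.96 − 1.981) = 0.492.
- Per-stratum: Φ(1.96 − 2.802) = 0.200.

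If the stratum without symptoms is 40% to 60% of the sample, power is 42% to 58% or 71% to 87%, so the chance of non-significance is about 42% to 58% or 13% to 29%.

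**What a non-significant result leaves open.** The 95% CI half-width is 1.96 × 1.010 = 1.98 days or 1.96 × 0.714 = 1.40 days. Even on the favourable reading, an observed harm of 1.3 days is non-significant while the interval reaches 1.3 + 1.4 = 2.7 days.

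**Non-inferiority instead, with candidate margins of 2 days and 1 point, one-sided 0.025, zero true difference.** Power per outcome is Φ(2/SE − 1.96).
- Whole-sample: Φ(1.981 − 1.96) = 0.508.
- Per-stratum: Φ(2.802 − 1.96) = 0.800.

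The chance of declaring non-inferiority when the harm equals the margin is 2.5% per outcome. If both outcomes must succeed and are independent, joint power is 0.508² = 0.26 or 0.80² = 0.64. Positive correlation raises it towards the single-outcome figure.

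On the whole-sample reading, 80% power per outcome needs 112 completers per arm in this stratum: 224 / 0.8 = 280 randomised there, and 280 / 0.5 = 560 overall.

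**The case against.** Several points on the other side have force.

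- **Power.** A reader might infer that this comparison is underpowered. The article does not establish that. The sex-difference paragraph takes 92 women and speaks of 23 per condition; 92 / 4 = 23 hints at four arm-by-stratum cells, and so possibly at power per stratum. The section also expects the mixed models to be more powerful than the ANOVA calculation. Low power holds only on the whole-sample reading.
- **Margins.** A reader might take 2 days and 1 point as the trial's own non-inferiority margins, or as differences it calls important. They are detectable differences. The only clinical remark is hedged, concerns smaller differences, and is attached to days; NODS has no rationale of its own.
- **Scope of the 49% and 20%.** They apply to one outcome at one visit. If support required non-significance on both outcomes and these were independent, false support at one visit would be 0.492² = 24% or 0.20² = 4%.
- **Consequence.** Nowhere does the article say that non-significance will be reported as proof of no harm or used to recommend G + MH for everyone. Hypothesis 2 is a prediction, and the Background gives this aim lesser weight.
- **Unseen analysis plan.** A margin may be set there, and its absence from an article is not in itself a fault.

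All of these stand as limits on size and consequence. None repairs the wording. The article states a prediction that non-significance fulfils and that benefit would refute. An analysis plan with a margin would be testing a different hypothesis from the one printed.

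**Conclusion.** The defect lies in how Hypothesis 2 is framed. Read as written, it would be supported by a result that cannot answer the no-harm question in the Background. The shared mixed model is not a separate error, since the same model yields the interval needed.

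The chance of non-significance despite a true harm of 2 days or 1 point is about 49% or 20% per outcome and time point, depending on what the stated power refers to. Both figures rest on the assumptions listed and on an SD solved from the plan's own power statement. The logical fault holds on either reading. The documents do not support going further, to a claim that the comparison is underpowered or that the trial has already set its margins.

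**What to change.** - Restate Hypothesis 2: among participants with K10 below 22, G + MH is non-inferior to G-only if the upper limit of the two-sided 95% CI for G + MH minus G-only lies below a pre-specified margin, higher scores being worse. If it does not, report the result as inconclusive.
- Justify the margin for each outcome. Two days per month and 1 NODS point are candidates, but the sponsor must give the clinical argument.
- Say whether three months, six months or both decide, since the present hypothesis names both, and whether both outcomes must meet their margins.
- State the SDs used and whether the 80% power refers to the whole sample or to each stratum.
- State the power at zero difference. At the candidate margins it is 51% (whole-sample reading) to 80% (per-stratum reading) per outcome. If both outcomes are required it is lower, down to about 26% to 64% if they are independent.

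The cost is a change of wording: model, data and sample size stay the same. The downside is that the trial may have to report that it could not settle this question.

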## Methods/design

### Study design

The proposed study is a two-arm, double blinded, parallel group RCT. See Fig. 1 below for a Consort Diagram summarizing this trial design.

**Fig. 1 Fig1:**
[figure not shown]
Overview of the proposed intervention trial

### Recruitment

Potential respondents will be recruited using online advertisements (e.g., Google adwords). The advertisement will ask if the person is concerned about their gambling and if they are interested in participating in a study that contains online help for gambling (with compensation provided). Interested participants will follow a link to a brief online survey to assess eligibility (details provided below). Those eligible and who provide informed consent will be sent an email with a unique link to the remaining baseline assessment. Participants who complete the baseline measures will then be randomized into one of the two Internet interventions described below (G-only versus G + MH). Only participants who complete the baseline survey via their unique link will be randomized and included in the trial. After completing the baseline survey, participants create a password which they then use to access the respective intervention websites through the study website portal. Research staff involved in the trial will not be informed of respondents’ group allocation during interventions or at follow-up. All participants will be followed-up at three- and six-month post-randomization using an online survey (an email invitation including a unique link will be sent to each participant). In order to promote retention, participants completing each of the follow-ups will be sent a $20 gift certificate from Amazon.ca (i.e., honorarium of $40 total). Ethics approval was obtained from the Research Ethics Boards of the Centre for Addiction and Mental Health (Canada) and the Australian National University (Australia).

#### Inclusion criteria

Primary inclusion criteria will follow those used in the ongoing trial by Hodgins et al. [26] and comprise being 18 years of age or older, perception of a gambling problem and scoring 3 or greater on the Problem Gambling Severity Index (PGSI) [28]. Prior treatment access will be measured but will not be used as an inclusion/exclusion criterion. This is because the intent of this trial is to evaluate the impact of the interventions in the extended range of potential community participants. Random assignment to condition with stratification will ensure that socio-demographic characteristics, such as treatment access, will be evenly distributed across conditions. Similarly, hazardous alcohol use and illicit drug consumption will be measured but will not be used as exclusion criteria. Finally, the trial will recruit participants with and without co-occurring mental health symptoms. We anticipate, based on prevalence data, that approximately 50 % of the sample will be experiencing co-occurring mental health symptoms. This will be established using the Kessler 10, with a score of 22 more indicating current psychological distress [29, 30].

### Randomization

Randomization will be conducted via an automated computer algorithm, set up by a researcher not involved in the day-to-day conduct of the trial according to ICH Guideline E9 [31]. Randomization will be stratified by age (18–35 years/over 36 years), sex (male/female), and prior use of treatment for problem gambling (have previously accessed treatment/have not accessed treatment).

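### Randomisation is not stratified by the baseline K10 group (22 or more / below 22), within which Hypotheses 1 and 2 compare the arms

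*Protocol article*

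**What the plan says.** The Randomization section gives a complete list of factors: age in two bands, then "sex (male/female), and prior use of treatment for problem gambling (have previously accessed treatment/have not accessed treatment". That makes three binary factors and eight strata. No mental health measure is among them.

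The Major research questions section states both arm comparisons by mental health status. Hypothesis 1 opens "For problem gamblers with co-occurring mental health symptoms, it is predicted that participants provided access to the G + MH website" and predicts better gambling outcomes with G + MH. Hypothesis 2 reads "Problem gamblers without co-occurring mental health symptoms will display no significant difference between the G-only and G + MH websites". Under Inclusion criteria, the status is defined as follows: "This will be established using the Kessler 10, with a score of 22 more indicating current psychological distress". The same section expects that "approximately 50 % of the sample will be experiencing co-occurring mental health symptoms".

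The Baseline assessment section includes the K10, and the Recruitment section fixes the order of events: "Participants who complete the baseline measures will then be randomized into one of the two Internet interventions". Allocation is by an automated computer algorithm (Randomization). The purpose of stratifying is described under Inclusion criteria: "Random assignment to condition with stratification will ensure that socio-demographic characteristics, such as treatment access, will be evenly distributed across conditions".

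**The concern.** The trial asks whether adding a mental health intervention helps gamblers with co-occurring symptoms and makes no difference to those without. Both questions are answered inside K10 groups, not in the whole sample. The protocol stratifies on three other factors but not on the one that defines these groups, although the algorithm could read it at allocation.

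Two kinds of chance imbalance are left open inside each K10 group. The number of participants per arm can drift from equality, which costs precision. The listed factors, held level across the whole sample, can also differ between arms within the group. Sex matters most here, because the Background names gender as a possible moderator of the benefit expected in participants with co-occurring symptoms. A visible imbalance in that subgroup would weaken the face validity of the result the trial is built to deliver.

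**Working it through.** **Inputs.** 280 randomised and about 224 followed at six months (Power analysis); about 50% at K10 of 22 or more (Inclusion criteria); about a third female (Power analysis). Assumed, because the article does not state them: 1:1 allocation with arm totals held at 140/140, and K10 status independent of the factor examined.

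**The plan's own figure.** 280 × (1 − 0.20) = 224, which reproduces. The article gives no figure for balance inside the K10 groups.

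**Arm split, higher K10 group.** Expected size is 0.50 × 280 = 140. With fixed arm totals, the number falling in one arm is hypergeometric (280 in total, 140 in the K10 group, 140 in the arm).
- SD = √(140 × 0.5 × 0.5 × 140/279) = 4.19.
- The 2.5% and 97.5% points are 62 and 78.
- P(arm sizes differ by 10 or more, i.e. 65/75 or worse) = 0.282.
- Efficiency relative to 70/70 at the 95% limit: 4 × 62 × 78 / 140² = 0.987. At 65/75: 4 × 65 × 75 / 140² = 0.995.
- If prevalence were 30% (84 participants), the range is 34/50 and the efficiency is 4 × 34 × 50 / 84² = 0.964.
- If allocation were simple randomisation, the range for 140 widens to 58/82, with efficiency 4 × 58 × 82 / 140² = 0.971.

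**Effect on power.** If 56 followed per arm in the subgroup gave 80% power, a followed split of 48/64 would give 79.2% and 45/67 would give 78.4%.

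**Stratified factors inside the higher K10 group.** Take about 70 per arm and a factor with prevalence p.
- With no stratification on the factor, the 95% limit for the between-arm difference is 1.96 × √(p(1 − p) × 2/70): 15.6 points at p = 0.33 and 16.6 at p = 0.50.
- The factor is in fact balanced across all 280. The K10 group is half of that balanced set, so the variance is multiplied by about 1 − 140/280 = 0.5.
- 1.96 × √(0.33 × 0.67 × 2/70 × 0.5) = 11.0 points; 1.96 × √(0.50 × 0.50 × 2/70 × 0.5) = 11.7 points.
- Simulation, with arms balanced within levels of the factor and a random 140 of 280 in the higher K10 group, gives 11.1 and 11.8 points.

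**Strata.** Adding K10 doubles the strata from 8 to 16; the mean stratum size falls from 280/8 = 35 to 280/16 = 17.5.

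**The case against.** The strongest reply is that very little is lost. K10 is measured before randomisation, so each within-group comparison is a valid randomised one. At the expected prevalence the precision loss at the 95% limit is about 1%. The 28% chance of a gap of 10 or more sounds worse than it is, since a 65/75 split keeps 99.5% of the efficiency. Residual imbalance can be handled by covariates, whose list an article may leave to the full analysis plan. The choice of stratifiers is ordinary design discretion. All of this stands, and it limits the point to a cheap improvement.

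A reader might infer more than the documents support, in four ways.
- That the subgroup comparisons are biased or confounded. They are not, because K10 precedes allocation.
- That the Inclusion criteria section is contradicted. Its statement concerns socio-demographic characteristics across conditions and promises nothing about balance within K10 groups.
- That every primary hypothesis is affected. Hypothesis 3 is also listed as primary, and it concerns involvement with the G-only intervention, not K10 status.
- That sex or prior treatment could differ by about 16 points. That figure ignores the existing stratification on these same factors.

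It is also fair to say that subgroup size matters more. If 80% power refers to all 224 followed (112 per arm), the same difference in 112 (56 per arm) has power of about Φ(2.80/√2 − 1.96) = 51%. Stratifying on K10 would not change that.

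The objection about sparse strata carries less weight: an average of 17.5 per stratum is a modest cost, and minimisation avoids it.

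**Conclusion.** The point holds as a design improvement of modest size. The variable that defines both arm-comparison hypotheses is available to the allocation algorithm and is left out of a stated list of stratifiers. What is lost is balance by design, not validity. In the higher K10 group the 95% range for the arm split is 62/78 (efficiency about 0.987), and sex or prior treatment can differ between arms by about 11 to 12 points at the 95% limit. These figures assume 1:1 allocation with equal arm totals, 50% prevalence, whole-sample balance on the listed factors, and K10 independent of those factors. At 30% prevalence the efficiency at the limit falls to about 0.96.

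**What to change.** Add K10 group (22 or more / below 22) as a stratification factor in the allocation algorithm, and name it in the Randomization section. Crossing it with sex, age and prior treatment fixes the arm sizes within each K10 group and also holds those three factors close to level there. It does not control covariates that are not stratified. If 16 strata are thought too sparse, use minimisation over the four factors. Include K10 and the stratification factors in the mixed models under Data analysis; if enrolment has begun, this is the part that can still be done.

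The cost is a small change to the randomisation program and a sentence in the protocol. The downside is about 17.5 participants per stratum on average, with fewer in rare cells. Power within the K10 groups needs to be addressed separately.
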